# mFOLFIRINOX versus mFOLFOX 6 as adjuvant treatment for high-risk stage III colon cancer - the FROST trial: study protocol for a multicenter, randomized controlled, phase II trial

**DOI:** 10.1186/s12885-024-11939-x

**Published:** 2024-03-29

**Keywords:** High-risk stage III colon cancer, Adjuvant chemotherapy, mFOLFIRINOX, mFOLFOX 6, Prognosis, Efficacy, Toxicity

## Abstract

**Background:**

High-risk stage III colon cancer has a considerably poorer prognosis than stage II and low-risk stage III colon cancers. Nevertheless, most guidelines recommend similar adjuvant treatment approaches for all these stages despite the dearth of research focusing on high-risk stage III colon cancer and the potential for improved prognosis with intensive adjuvant treatment. Given the the proven efficacy of triplet chemotherapy in metastatic colorectal cancer treatment, the goal of this study is to evaluate the oncologic efficacy and safety of mFOLFIRINOX in comparison to those of the current standard of care, mFOLFOX 6, as an adjuvant treatment for patients diagnosed with high-risk stage III colon cancer after radical resection.

**Methods:**

This multicenter, randomized (1:1), open-label, phase II trial will assess and compare the effectiveness and toxicity of mFOLFIRINOX and mFOLFOX 6 in patients with high-risk stage III colon cancer after radical resection. The goal of the trial is to enroll 312 eligible patients, from 11 institutes, aged between 20 and 70 years, with an Eastern Cooperative Oncology Group (ECOG) performance status of 0–2, or between 70 and 75 with an ECOG performance status of 0. Patients will be randomized into two arms - Arm A, the experimental arm, and Arm B, the reference arm - and will receive 12 cycles of mFOLFIRINOX and mFOLFOX 6 every 2 weeks, respectively. The primary endpoint of this study is the 3-year disease-free survival, and secondary endpoints include the 3-year overall survival and treatment toxicity.

**Discussion:**

The Frost trial would help determine the oncologic efficacy and safety of adjuvant triplet chemotherapy for high-risk stage III colon cancers and ultimately improve prognoses.

**Trial registration:**

ClinicalTrials.gov NCT05179889, registered on 17 December 2021.

## Background

Based on numerous studies conducted since the publication of the MOSAIC trial in 2004 [1–3], the standard adjuvant treatment for stage III colon cancer (CC) following radical resection has evolved to involve doublet therapy consisting of oxaliplatin and 5-fluoropyromidine (5-FU). The addition of irinotecan to 5-FU for the treatment of radically resected stage III CC did not demonstrate improved survival compared to that achieved with 5-FU alone [4–6]; additionally, the combination of targeted agents, such as cetuximab or bevacizumab, with chemotherapy also failed to demonstrate remarkable oncological benefits [7–10]. Consequently, most international guidelines recommended a 6-month regimen of FOLFOX (oxaliplatin and 5-FU) or CAPOX (oxaliplatin and capecitabine) for adjuvant treatment of stage III CC.

Recently, the findings of the IDEA collaboration study [11] highlighted equivalent disease-free survival (DFS) rates with 3 months of CAPOX and with 6 months of CAPOX and substantially reduced toxicity with the former. Consequently, the National Comprehensive Cancer Network guidelines currently suggest 3 months of CAPOX or 3 or 6 months of FOLFOX as options for treatment of low-risk stage III (pT1-3N1) CC and 3–6 months of CAPOX or 6 months of FOLFOX for high-risk stage III (pT4N1-2 or TanyN2) CC treatment.

However, a paucity of information remains for patients with high-risk stage III CC, and research exploring more extensive adjuvant treatment options is scarce. According to the current guidelines, 3 months of CAPOX should be considered the first option for all high-risk stage II CC, low-risk stage III CC, and high-risk stage III CC. However, these patient groups exhibit considerably different prognoses. The IDEA study reported a 3-year DFS rate of 62.7–64% for patients with high-risk stage III CC compared to the 83.1–83.3% rate for patients with low-risk stage III CC [11]. Consequently, there is a need for research on more extensive adjuvant treatments for patients with high-risk stage III CC, even after successful R0 resection.

Personalized medicine is a crucial concept in the current treatment paradigm for metastatic colorectal cancer, and its extension to the management of non-metastatic colorectal cancer, particularly high-risk stage III CC, which carries high potential of progression to metastatic disease, is warranted. Therefore, it is essential to evaluate whether the triplet regimen of mFOLFIRINOX (oxaliplatin, irinotecan, and 5-FU), which has recently demonstrated superior efficacy in patients with unresectable metastatic colorectal cancer, can improve the prognosis of patients with high-risk stage 3 CC. Although a prospective single-arm study with a small sample size reported the safety and efficacy of triplet chemotherapy for locally advanced, resectable CC [12], and a randomized prospective study regarding a conventional regimen of triplet chemotherapy as an adjuvant treatment for high-risk stage III CC has been initiated in overseas [13], randomized controlled trials investigating the modified regimen of mFOLFIRINOX are lacking.

Therefore, the goal of this study is to evaluate the oncologic efficacy and safety of mFOLFIRINOX in comparison to those of the current standard of care, mFOLFOX 6, as an adjuvant treatment for patients diagnosed with high-risk stage III colon cancer after radical resection.

## Methods

### Study design

This multicenter, randomized (1:1), open-label, phase II trial assesses the effectiveness and toxicity of mFOLFIRINOX compared to those of mFOLFOX-6 as an adjuvant treatment for patients with high-risk stage III CC. Patient enrollment will be performed across 11 tertiary hospitals in one country. The flow-diagram of the study is presented in Fig. 1.

**Fig. 1 Fig1:**
[figure not shown]
Flow-diagram of FROST trial, PS, performance score

### Study population

#### Inclusion criteria

Age between 20 and 70 years with an Eastern Cooperative Oncology Group (ECOG) performance status of 2 or lower, or age between 71 and 75 years with an ECOG performance status of 0.Pathologically confirmed high-risk stage III CC (pT4N1-2 or pTanyN2).Successful R0 resection for CC above the upper rectum within 60 d prior to screening.Adequate organ functions, as determined by laboratory tests after operation and before screening.
absolute neutrophil count ≥ 2 × 10^6^ cells/mL.hemoglobin ≥ 9.0 g/dL, platelet count ≥ 100 × 10^6^ cells/mL.alanine aminotransferase/aspartate aminotransferase ≤ 2.5 times the upper limit of normal (ULN).serum total bilirubin levels ≤ 1.5 times the ULN.alkaline phosphatase levels ≤ 2.5 times the ULN.serum creatinine levels ≤ 1.5 times the ULN or creatinine clearance > 50 mL/min based on the Cockcroft-Gault formula.
Ability to understand and willingness to provide written informed consent.A life expectancy of at least 5 years.

#### Exclusion criteria

Presence of distant metastases.Lower and middle rectal cancer requiring radiotherapy.Postoperative complications of grade 4 or higher according to the Clavien-Dindo classification.Underlying medical or systemic conditions that impede chemotherapy administration.Known hypersensitivity to all relevant tests or treatment components.Familial adenomatous polyposis or hereditary nonpolyposis colorectal cancer.Inflammatory bowel disease.Presence of other incurable prior malignancies.Pregnancy (confirmed by serum beta-human chorionic gonadotropin test) or lactation.Any other circumstances that, at the discretion of the investigator, might result in exclusion from the study.

### Interventions

#### Treatment and toxicity assessment

Patients will be randomized into two treatment arms - Arm A, the experimental arm, and arm B, the reference arm - and will receive 12 cycles of mFOLFIRINOX or mFOLFOX 6 every 2 weeks, respectively. The mFOLFIRINOX regimen consists of intravenous irinotecan 150 mg/m^2^, oxaliplatin 85 mg/m^2^, and leucovorin 400 (or levoleucovorin 200) mg/m^2^ on day 1 and continuous infusion of 5-FU 1200 mg/m^2^/d intravenously for the next 2 d (total 2400 mg/m^2^ over 48 h). The mFOLFOX 6 regimen consists of intravenous oxaliplatin 85 mg/m^2^, leucovorin 400 (or levoleucovorin 200) mg/m^2^, and bolus 5-FU 400 mg/m^2^ on day 1 and continuous infusion of 5-FU 1200 mg/m^2^/d intravenously for the next 2 d (total 2400 mg/m^2^ over 48 h).

Although there is no absolute contraindication with other treatments, caution will be exercised when co-administering these with drugs that might cause toxicities such as cardiotoxicity, hepatotoxicity, nephrotoxicity, myelodysfunction, and neurotoxicity. Toxicity will be monitored by taking the patient history and conducting laboratory tests before the initiation of the next cycle of treatment.

The drug dose could be adjusted at the discretion of the investigator, if necessary, because of toxicity, and the reduced dose could be sustained for subsequent cycles. Discontinuation will be considered after sustained toxicity despite dose reduction and management, recurrence during treatment, or on patient request.

#### Recurrence assessment

Recurrent assessment, including carcinoembryonic antigen measurement, abdominopelvic computer tomography (CT), and chest radiography or CT, will be performed after every 4 cycles of treatment and postoperatively every 4 months for 2 years and every 6 months for the next 3 years. The modality and interval of evaluation could be added and adjusted at the discretion of the investigator, if necessary. If recurrence is detected during treatment, study treatment will be discontinued and a standard personalized treatment will be conducted. If recurrence is detected during the follow-up period, a standard personalized treatment will be conducted. The participant timeline is presented in Table 1.

**Table 1 Tab1:** Timeline of enrollment, intervention, assessment, and surveillance in FROST trial

Visit^1^	Screening	Chemotherapy period			Follow-up period	
		C1D1	C2–3D1 C5–7D1 C9–11D1	C4D1 C8D1 C12D1	F1–5	F6, F7
**Interval**			2 weeks (-4 d/+7 d)		4 months (-14/+30 d)	6 months (-14/+30 d)
Informed consent	X					
Screening number	X					
Complication check^2^	X					
Criteria check	X	X				
Randomization		X				
Performance status check	X	X	X	X		
Medical history and physical examination	X	X	X	X	X	X
Height, weight, BSA^3^		X	X	X		
Vital sign^4^	X	X	X	X		
Laboratory test^5^	X	X	X	X	X	X
Pregnancy test ^6^	X		X (even-numbered cycles)			
Treatment		X	X		X	
CEA^7^	X			X	X	X
Imaging study^8^				X	X	X
Colonoscopy^9^					X	X
**Safety assessment**		X	X	X		
**Efficacy assessment**				X	X	X

^1^The next visit is based on the previous visit date. In the treatment phase, the first day of each treatment cycle (e.g., C1D1, C2D1…) is the reference date

^2^Postoperative complications: Evaluate complications within 30 d after surgery according to the Clavien-Dindo Classification

^3^BSA (body surface area)

^4^Vital signs include blood pressure, heart rate, respiratory rate, and body temperature

^5^Laboratory tests include complete blood count, liver and kidney function tests, and electrolytes

^6^Pregnancy test (serum beta-human chorionic gonadotropin test): Performed on even-numbered cycles (C2, 4, 6, 8, 10, 12) only for fertile women

^7^CEA (carcinoembryonic antigen): The first test performed before surgery and during the postoperative screening period

^8^Imaging studies include abdominopelvic computed tomography (CT) and chest radiography (C4, C8, F2, F4, F6) or CT (C12, F1, F3, F5, F7)

^9^Colonoscopy is recommended in F1 and F7

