### Endpoints

#### Primary endpoint

The primary endpoint of the study is the 3-year DFS rate based on intention-to-treat analysis, which is defined as the proportion of patients who were alive without recurrence at 3 years from the date of surgery. It will be calculated using the time from the date of surgery to the date of recurrence detection, death, or the last follow-up. In cases where patients are lost before the 3-year mark, their data will be censored as of the last follow-up date and assessed accordingly.

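### Recurrence imaging is timed by cycles given and chained visits, so when a DFS event can be detected depends on delay and early stopping; one common imaging calendar would remove a small, avoidable bias of uncertain sign.

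*Protocol article*

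**What the plan says.** Recurrence assessment, in the Interventions section, states that CEA and imaging "will be performed after every 4 cycles of treatment" and, in the same sentence, "postoperatively every 4 months for 2 years and every 6 months for the next 3 years". Investigators may depart from this: "The modality and interval of evaluation could be added and adjusted at the discretion of the investigator, if necessary".

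Table 1 puts treatment-phase imaging in the C4, C8 and C12 column only, followed by F1 to F7. Footnote 8 assigns the chest modality visit by visit: "chest radiography (C4, C8, F2, F4, F6) or CT (C12, F1, F3, F5, F7". Footnote 1 sets the clock: "The next visit is based on the previous visit date", and "In the treatment phase, the first day of each treatment cycle (e.g., C1D1, C2D1…) is the reference date". Cycles are 2 weeks apart (-4/+7 days), F1 to F5 are 4 months apart and F6 and F7 are 6 months apart (-14/+30 days). The table shows no end-of-treatment scan and no fixed-date scan for a patient who stops early.

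Treatment and toxicity assessment foresees early stopping: "Discontinuation will be considered after sustained toxicity despite dose reduction and management, recurrence during treatment, or on patient request". Primary endpoint defines a 3-year DFS rate measured from surgery, with time running to "the date of recurrence detection, death, or the last follow-up".

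**The concern.** A recurrence enters the DFS analysis on the day it is found. Under Table 1 the opportunities to find it follow the number and timing of cycles received, which is an outcome after randomization. Arm A adds irinotecan, while only arm B has a 5-FU bolus, and the protocol makes treatment discontinuation and delivered dose secondary endpoints. A difference in adherence between arms is therefore plausible, though the article states none. If it occurs, the arms are observed on different calendars even when every site follows the schedule exactly. What is at stake is comparability of the DFS times and, to a lesser degree, of the 3-year rate.

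**Working it through.** **Inputs.** From Table 1: 14-day cycles (up to +7 days), F1 to F5 every 4 months (121.75 d), F6 and F7 every 6 months (182.6 d). From Primary endpoint: landmark at 3 years (1096 d) from surgery. From Sample size calculation: 3-year DFS 65% and 77.5%. Assumed: C1D1 falls g = 28, 42 or 60 days after surgery; F1 is counted from the last cycle given; recurrence is found only at scans.

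**1. Schedule for a completer.** C(k)D1 = 14(k-1), so C4, C8 and C12 fall on days 42, 98 and 154 from C1D1, 56 days apart.

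**2. Early stopping.** F1 = 14(k-1) + 121.75, where k is the last cycle given.
- Stop after C7: 84 + 122 = day 206, where the C8 scan would have been day 98. That is 108 days later, and the gap since the C4 scan is 206 - 42 = 164 d instead of 56 d.
- Stop after C3: 28 + 122 = day 150, where the first scan would have been day 42.
- Later scans then come sooner. A completer's F1 is on day 154 + 122 = 276, so after stopping at C7 it comes 70 days earlier.

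**3. Delay.** With every cycle 7 days late, all within window, C8 moves from day 98 to 7 × 21 = 147 and C12 from 154 to 11 × 21 = 231. C12 and every later visit move by 77 days.

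**4. Last scan before the landmark.** F6 = last cycle + 5 × 121.75 + 182.6 = last cycle + 791; F7 = last cycle + 974. Days from surgery:

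| Course of treatment | g = 28 | g = 42 | g = 60 |
|---|---|---|---|
| 12 cycles on time (g + 154 + 791) | F6, 973 | F6, 987 | F6, 1005 |
| 12 cycles, each 7 d late (+77) | F6, 1050 | F6, 1064 | F6, 1082 |
| Stop after C6 | F7, 1072 | F7, 1086 | F6, 921 (F7 at 1104 is past 1096) |
| Stop after C8 | F6, 917 | F6, 931 | F6, 949 |

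F7 falls before day 1096 when the last cycle is no later than C7, C6 or C5 for g = 28, 42 or 60. So cycles received decide whether F6 or F7 is the last scan before 3 years.

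**5. Effect on the 3-year rate, with equal true DFS in both arms.** With exponential DFS, observed rate = S^(t/1096), where S is the true 3-year rate and t the day of the last scan before the landmark.
- One arm on time, the other 7 d late at every cycle, g = 28, S = 0.65: 0.65^(973/1096) = 68.2% against 0.65^(1050/1096) = 66.2%, so the delayed arm is about 2.0 points lower. At S = 0.775: 79.7% against 78.3%, or -1.4 points. Delays of 0.25 and 0.5 week per cycle give -0.5 and -1.0 points at 65%.
- 20% of one arm stop after C6, S = 0.65. For g = 28: 0.65^(1072/1096) = 65.6% in stoppers against 68.2%, and 0.20 × (-2.6) = -0.5 points. For g = 60: 0.65^(921/1096) = 69.6% against 0.65^(1005/1096) = 67.4%, and 0.20 × 2.3 = about +0.5 points. The sign turns on the time from surgery to C1.

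**6. Surgery-based reading of the text.** Scans at months 4, 8, 12, 16, 20, 24, 30 and 36 do not depend on cycles and include the landmark, so this bias is zero. Table 1 differs: its follow-up visits are chained and end 5 × 4 + 2 × 6 = 32 months after the last cycle, whereas the text promises 5 years.

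**The case against.** The strongest reply is that the sentence on cycle-linked scans also contains a postoperative 4-monthly clause. Read as a calendar from surgery, it keeps early stoppers under observation and gives everyone a month-36 scan. That reading is open, and on it the problem largely disappears. But a site working from Table 1 would not follow it, so the two still have to be reconciled. The discretion clause would let an investigator scan a stopper on time, but does not require it.

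Second, the article is a condensed account. It does not say that F1 is counted from the last cycle given when treatment stops early, and the full protocol may settle this. The early-stopping figures are conditional on that inference. The delay figures follow from footnote 1 directly.

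Third, a reader might infer that late scanning flatters arm A. The documents do not support this for the primary endpoint. Being late applies only to the next scan after stopping. At the landmark, a stopper whose F7 precedes 3 years is last scanned at g + 974 days or later, closer to 3 years than a completer's F6 at g + 945. Delay likewise moves F6 towards the landmark, and both lower the observed rate.

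A reader might also infer that the 3-year status of early stoppers goes unobserved. That holds only if Table 1 overrides the text, and the follow-up windows of up to +30 days can carry F7 past 3 years.

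Fourth, no discontinuation or delay rates are given. The Discussion's remark on poorer completion concerns the conventional triplet, not mFOLFIRINOX against mFOLFOX 6. A difference between arms is a reasonable possibility, not a stated fact.

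**Conclusion.** The point holds as a modest, avoidable design weakness. Treatment-phase imaging follows cycle number, visits are chained, and events are dated at detection, so the chance to detect the primary event depends on adherence. For individual patients the shift is material: about 108 days for the next scan after stopping at C7, and 77 days from C12 onward with maximal in-window delay. DFS times early in follow-up are therefore the more affected. For the 3-year rate, the largest effect in the scenarios examined is about 2 points against a 12.5-point target. That figure puts every patient in one arm, and none in the other, at the window limit for every cycle, with all recurrences found at scans. The sign varies with stopping, and delay works against the delayed arm. The times from surgery to C1, the delays and the 20% stopping rate are assumptions. The documents do not show that either arm is favoured.

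**What to change.** Reconcile the Recurrence assessment text and Table 1 into one imaging calendar:
- Use one origin for both arms: surgery, which is the DFS origin, or randomization.
- Fix the assessment dates regardless of cycles given, delayed or stopped. The treatment-phase scans can sit at the weeks where C4, C8 and C12 would nominally fall.
- State that a patient who stops treatment without recurrence stays on the same calendar.
- Include a scan at 36 months from surgery.

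This changes when recurrence is looked for and leaves treatment untouched. The cost is wording in the protocol and Table 1. Putting treatment-phase scans at the nominal weeks leaves their number unchanged for completers. Some scans will no longer coincide with a chemotherapy visit, and early stoppers attend for scans already planned for others. With 19 of 312 patients enrolled by July 2023 (Trial status), a change at that point would have covered nearly the whole sample.

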### Data management

To conceal personal information, the allocation sequence employs the double-digit participant number and the three-digit institute number, which are automatically generated on the eCRF in order of registered participants, based on the date of acquisition of informed consent. Access to the eCRF will be exclusively granted to registered researchers involved in this study. Screening, obtaining informed consent, enrollment, registration, and data collection will be conducted by investigators or qualified clinical research coordinators. Blinding will not be implemented because of the open-label nature of the study.

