### Statistical analysis

#### Sample size calculation

Based on previous research [11], it is anticipated that the experimental group receiving mFOLFIRINOX as adjuvant treatment will achieve a 3-year DFS rate of 77.5%, with an improvement of 12.5% compared to the control group, which is estimated to have a 65% DFS rate. To determine the sample size for the study, a power analysis was performed using the PASS (Power Analysis and Sample Size) 13.0 program (NCSS, LLC, Kaysville, Utah, USA). The calculations indicated that a minimum of 156 subjects will be required for each treatment arm, considering the desired statistical power of 80%, the significance level of 10%, and the dropout rate of 10%. Therefore, a total of 312 subjects, equally stratified and randomized, will be enrolled to ensure adequate statistical power and robust results.

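### The investigator, who knows the arm, may adjust the modality and interval of scheduled recurrence imaging, so the 3-year DFS event could be looked for differently in the two arms

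*Protocol article*

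**What the plan says.** All references are to the protocol article.

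- **Recurrence assessment.** Both arms share one schedule: CEA, abdominopelvic CT and chest imaging after every four cycles and then "postoperatively every 4 months for 2 years and every 6 months for the next 3 years". Table 1 gives follow-up windows of -14/+30 days. In its footnote 8, only the chest examination changes between radiography and CT from visit to visit; abdominopelvic CT belongs to every imaging visit. F6 has chest radiography, while F5 and F7 have chest CT. Footnote 1 chains the visits: "The next visit is based on the previous visit date".
- **The discretion**, in the same section: "The modality and interval of evaluation could be added and adjusted at the discretion of the investigator, if necessary".
- **Data management.** "Blinding will not be implemented because of the open-label nature of the study".
- **Primary endpoint.** The 3-year DFS rate is "defined as the proportion of patients who were alive without recurrence at 3 years from the date of surgery". On timing: "It will be calculated using the time from the date of surgery to the date of recurrence detection, death, or the last follow-up".
- **Sample size calculation.** The experimental arm is expected to reach 77.5%, 12.5 points above the control arm, "which is estimated to have a 65% DFS rate".

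**The concern.** A recurrence enters the primary endpoint on the day it is found, so its date depends on when and how someone looks. The person allowed to change both knows the treatment. Extra imaging on clinical suspicion is ordinary care and is not the problem. The difficulty is that the permission also covers adjustment: a routine interval may be lengthened, or a scheduled modality replaced, and the only condition is necessity. By contrast, the article ties discretionary dose changes to toxicity.

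If such changes were made more often in one arm, that arm's recurrences would be dated later or earlier than the other's, and the observed 3-year DFS rates would differ without any difference in disease. Randomization balances the patients, not the way they are followed afterwards. A landmark rate is sensitive to this when the landmark lies between two scans, because a recurrence found just after month 36 does not count.

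**Working it through.** The plan gives no figure for this effect, so there is none to reproduce. The following is an illustration of size.

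**Inputs from the article:** control 3-year DFS 65%; target difference 12.5 points; 12 two-weekly cycles; F1 to F5 at 4-month and F6 to F7 at 6-month intervals, each counted from the previous visit; 156 patients per arm with 10% dropout.

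**Assumptions (not in the article):** constant hazard; recurrence found only at scans, and always found there; patients remain in follow-up beyond month 36; C1D1 falls 0 to 3 months after surgery (0 is a limiting case, since DFS counts from surgery).

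**Step 1, hazard.** λ = -ln(0.65)/36 = 0.01197 per month, and S(t) = exp(-λt).

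**Step 2, visit times from surgery.** C12D1 comes 11 × 2 = 22 weeks, or 5.06 months, after C1D1. F5 is 5 × 4 = 20 months after C12, F6 is 26 and F7 is 32 months after it.

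**Step 3, losing F6.** If F6 slips past month 36 or is omitted, F5 is the last scan that counts. Observed 3-year DFS in those patients becomes S(F5) instead of S(F6).

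| C1D1 after surgery | F5 | F6 | F7 | S(F5) | S(F6) | Rise |
|---|---|---|---|---|---|---|
| 0 months | 25.1 | 31.1 | 37.1 | 74.1% | 69.0% | 5.1 points |
| 1 month | 26.1 | 32.1 | 38.1 | 73.2% | 68.1% | 5.1 points |
| 2 months | 27.1 | 33.1 | 39.1 | 72.3% | 67.3% | 5.0 points |
| 3 months | 28.1 | 34.1 | 40.1 | 71.5% | 66.5% | 5.0 points |

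Month 36 lies between F6 and F7 in every row. With C1D1 at 1 to 3 months, F6 has 36 - 32.1 = 3.9 down to 36 - 34.1 = 1.9 months of slack, so a total slip of about 2 to 4 months anywhere in the chain moves it past the landmark. If the schedule is instead read as counted from surgery (scans at 24, 30 and 36 months), losing the month-36 scan gives S(30) - 65% = 69.8% - 65.0% = 4.8 points, which is much the same.

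**Step 4, dilution.** Bias in the arm difference = share of one arm affected × rise. The shares are assumptions.

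| Share affected in one arm only | Bias | As part of 12.5 points |
|---|---|---|
| 10% | 0.5 points | 4% |
| 30% | 1.5 points | 12% |
| 50% | 2.5 to 2.6 points | about 20% |

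**Step 5, against sampling error.** With 156 × 0.9 ≈ 140 evaluable per arm, the standard error of the planned difference is √(0.65 × 0.35/140 + 0.775 × 0.225/140) = 5.4 points. A bias of 1.5 points is about 0.3 standard errors.

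**Step 6, the opposite change.** An extra scan at month 36 in one arm only, with F6 the last scan in the other, lowers observed DFS by S(F6) - 65% = 3.1, 2.3 or 1.5 points for C1D1 at 1, 2 or 3 months. These are upper bounds for those timings, because they assume that every patient in the arm has the extra scan.

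**The case against.** The strongest reply is that the default schedule is identical in both arms and that the discretion is qualified by necessity. The article is also a condensed account of a protocol (version 4.0) that is not shown. Triggers for unscheduled imaging, CRF fields, independent reading of scans and sensitivity analyses commonly sit in the full protocol or the SAP. That stands, and none of those absences is held against the plan here. What remains is a stated rule on how the primary event is ascertained, and that rule permits adjustment as well as addition.

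The modality part is limited. Abdominopelvic CT is scheduled at every imaging visit, and the default alternation of radiography and CT concerns the chest alone. The wording would still allow either to be changed.

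The size is constructed. It rests on a constant hazard, assumed visit times and an assumed imbalance, and it ignores recurrences found between scans through symptoms or CEA. At 30% affected it is small beside the sampling error.

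Stronger readings are tempting, and the documents support none of them:

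- A reader might infer that the comparison is biased, or biased towards mFOLFIRINOX. Nothing in the article says that either arm will be scanned less. If the experimental arm were followed more closely, the apparent benefit would shrink.
- A reader might infer that no analysis could repair the damage. That is too absolute. If scan dates are recorded, interval-censored methods deal with part of it. They do not correct for differing sensitivity of modalities, and they need assumptions to fill in status at month 36.

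**Conclusion.** The concern holds as a weakness in a stated rule. The plan as written lets the timing and modality of scheduled recurrence assessment differ by arm, in an open-label trial whose primary event is dated at detection and whose landmark falls between two scans. Differential ascertainment is possible rather than shown.

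Under the stated assumptions the effect is about 5 points in patients who lose the F6 scan. The 5-point figure barely depends on when chemotherapy starts. The effect on the arm difference depends almost entirely on the assumed imbalance, and the documents give no basis for choosing a value within that range. This merits an amendment because the remedy is cheap; it does not invalidate the design.

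**What to change.** Amend the sentence in the Recurrence assessment section so that, in both arms, the scheduled efficacy assessments are kept within the Table 1 windows and with at least the scheduled modality, and investigator discretion only adds assessments. The clinical reasons for extra imaging stay with the investigator. Record every unscheduled, delayed or changed scan with its date, modality and reason.

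Report the number, timing and modality of scans by arm. Add a sensitivity analysis of DFS that treats each recurrence as interval-censored between the last clear scan and the scan that found it. This is preferable to re-dating recurrences from unscheduled scans to the next scheduled visit. Re-dating does nothing about delayed scans, and because F7 falls after month 36 it would move recurrences found between F6 and month 36 out of the 3-year rate.

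Two limits remain. Added scans can still be unequal between arms. Because visits are chained, the +30-day allowance can also accumulate: six intervals to F6 give up to 6 × 30 = 180 days. The recorded dates, the report by arm and the interval-censored analysis are there to show and partly absorb both.

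The cost is one amended sentence, one CRF field and some loss of site freedom to move routine scans. The Trial status section reports 19 of 312 patients enrolled as of July 2023, so at that date few would have been followed under the present wording.
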